## Abstract

**Background:**

Childhood adversities, such as poor parental practices, exposure to violence, and risk behaviours strongly impact children’s future mental and behavioural problems. Adversities affect families living in disadvantaged environments and low- and middle-income countries (LMICs) to a greater extent than in high-income countries. Parenting programmes are an effective way to alleviate them, although their outreach and scalability is still limited in LMICs.

**Methods/design:**

A multi-site randomised controlled trial will be conducted in North Macedonia, Republic of Moldova and Romania to test the efficacy and cost-effectiveness of an optimised version of the promising Parenting for Lifelong Health Programme for Young Children (PLH-YC, 5 sessions), against a standard lecture on parenting issues (control group, 1 session). At least 864 participants who report having children between 2 and 9 years old who display elevated levels of behavioural difficulties will be randomised on a 1:1 basis to the intervention and control groups. The primary outcome will consist of parent report of child oppositional aggressive behaviour. Post-test (four months) and follow-up (12 months) assessments will provide information on short- and longer-term effects of PLH-YC compared to the parenting lecture in the control group.

**Discussion:**

This randomised trial will test the efficacy of PLH-YC in alleviating child behavioural problems and assess the cost-effectiveness, transportability across three different cultural contexts, and potential for scalability of the programme.

**Trial registration:**

ClinicalTrials.gov., Registration number: NCT04721730 (https://clinicaltrials.gov/ct2/show/NCT04721730). Registered 13.01.2021

**Supplementary Information:**

The online version contains supplementary material available at 10.1186/s13063-021-05817-1.

## Background

The health of children and adolescents plays a central role in the public health agenda with salutary results: morbidity and mortality from communicable diseases have steadily decreased since 1990 [1]. However, the World Health Organization (WHO) cautioned that, despite being preventable, youth mental health problems continue to be overlooked, leaving youth unable to achieve their full potential as adults [2]. Globally, between 10 and 20% of children suffer from mental health problems, which account for an estimated 16% of the global burden of disease and injury in those aged 10–19 years [3]. Much of the burden associated with impaired mental health is carried by young people in low- and middle-income countries (LMICs), who make up roughly 85% of the total child and adolescent population in the world [4]. In the European Region, the proportion of adolescents from LMICs who struggle with emotional difficulties is generally higher than of those facing the same difficulties in high-income countries (HIC). For instance, almost 33% of the Romanian, 26% of the Moldovan, and 19% of the North Macedonian adolescents, aged 11 to 15, reported feeling low more than once a week, compared to 13% on average across the 45 countries included in the survey [5].

Socio-economic disadvantages and child mental health tend to intersect, through exposure to immediate adversity that impacts on parenting, caregivers’ own mental health and relational issues, and their risk behaviours, increasing the risk of child abuse [6–9]. The Adverse Childhood Experiences Study (ACE) [10] conducted in eight LMICs illustrated this with 30% of Moldovan, 27% of Romanian, and 21% of North Macedonian children subjected to physical abuse compared to 4–16% in HICs [11]. In addition to exposure to physical abuse, 22% of children in Romania witness someone in the household having an alcohol problem and 14% live with a depressed or suicidal household member. In North Macedonia, emotional neglect (17%), followed by problematic alcohol use (9%), and depression/suicidal ideation in one household member (7%) were the top three most frequently mentioned ACEs. Exposure to multiple adversities has exponential effects on future adults: youngsters exposed to physical abuse are more likely to start smoking early, experiment with high-risk drugs, run away from home, attempt suicide, or engage in sexual risk behaviours [12–15].

Despite challenges, many children who grow up living with adversity become healthy adults. The protective role of an emotionally warm and competent caring system in helping children to overcome adversities and in fostering social and emotional regulation skills is well-established [16]. Parenting in disadvantaged communities, however, is fraught with difficulties that undermine both parents’ own mental health and their ability to provide protective parenting. In addition, the exposure of children to community adversity that increases child behaviour problems is, in itself, a factor that may elicit harsh, inconsistent parental practices [17–19]. Parenting programmes are key to assisting caregivers who raise families affected by adversities and have been shown to be effective in improving both parental practices [20, 21] and reducing child maltreatment and children’s emotional and behavioural problems [21–23]. Some programme components appear particularly effective in reducing disruptive behaviours in children: positive reinforcement, praising desired behaviours, and applying natural or logical consequences [24]. These components are shared across many different evidence-based parenting programmes, having their roots in social learning theory and the programme design approach of Hanf [25]. However, they are usually costly and difficult to transfer to, and scale-up in, LMICs [26]. The risk in rolling out such programmes is that their cost may prevent them from reaching the most disadvantaged individuals and communities, thus potentially widening the social inequality gap by being accessible mostly to more well-off families and communities [27]. This would represent a huge missed opportunity. There is encouraging evidence that the components of these interventions can be transposed and successfully adapted to LMICs provided that the cultural particularities of these countries are taken into consideration whilst retaining their fundamental core principles [28, 29]. Strong involvement of local communities is also key to both successful adaptation and scale-up [30].

The existing evidence base highlights opportunities to address the mental health problems of children in LMICs, but also warns about milestones that need to be reached. There are still relatively few rigorously conducted randomised controlled trials (RCTs) of structured parenting programmes in LMICs [31], and it is unclear whether or how the accumulation of adversity interacts with programme components in enhancing or hampering beneficial effects. There are even fewer data on whether, and how, these interventions work across different contexts and in different LMICs, and whether they are similarly cost-effective [29]. Multi-site RCTs, like the present one, to be conducted in North Macedonia, Republic of Moldova and Romania, provide an opportunity to address these important questions and provide high-quality data to support local decision-making and service consolidation.

### Overview and aims of the present study

The present study is part of a cross-country project financed by the European Commission (Project Number 779318), called “Prevention of Child Mental Health Problems in Southeastern Europe - Adapt, Optimise, Test, and Extend Parenting for Lifelong Health (RISE).” The programme tested in this project is an adaptation of the Parenting for Lifelong Health for Young Children (PLH-YC) programme, for parents of children between 2 and 9 years old. PLH is a joint initiative of the World Health Organization, UNICEF, Clowns Without Borders South Africa, and a number of universities around the world, targeting families of infants, children, and adolescents to reduce violence against children and improve child wellbeing. It focuses on consolidating parenting skills involved in relationship building (spending one-to-one time with children and emotional coaching), positive reinforcement of children’s adaptive behaviours (praising and rewarding, providing positive instructions, setting household rules, and routines) and teaching positive discipline strategies (ignoring negative attention seeking and unreasonable demands, time-out, and establishing reasonable consequences for inappropriate behaviours) [32]. The programme is designed to be accessible and easy to integrate into communities’ existing childcare or social services and requires no particular professional background, although a PLH training programme for facilitators is strongly encouraged. PLH was tested in LMIC with promising results in South Africa [33, 34] and the Philippines [35].

The RISE project uses the Multiphase Optimisation Strategy (MOST) framework to optimise the intervention by taking into consideration effectiveness, cost-effectiveness, and scalability [36] in these three LMICs. The project aim is threefold: Phase 1 (Preparation) to implement a systematic empirical process in order to adapt contents and materials of PLH-YC for use in the three LMICs (surface adaptation) and test their feasibility in a small pre-post study; Phase 2 (Optimisation) to test the efficacy and cost-effectiveness of different programme components in order to select the most effective and cost-effective components for an optimised intervention; Phase 3 (Evaluation) to test the optimised intervention (identified in Phase 2) in an RCT conducted in the three LMICs, taking into consideration the broader socio-economical, cultural, and contextual factors relevant within, and across, the three countries. The protocols for the first two phases (Preparation and Optimisation) were presented in detail elsewhere [32, 37].

The present protocol draws on the third objective of RISE, as part of the Evaluation phase of MOST, by describing in detail the multi-site RCT.

The primary aims and subsequent trial hypotheses are to:
Test the effectiveness of the optimised PLH-YC programme in comparison to a parenting lecture in a multi-site RCT in three Southeastern European countries: North Macedonia, Republic of Moldova and Romania on the *primary outcome* child oppositional aggressive behaviour assessed by parent report of the level of child aggressive behaviour, prevalence of child externalising disorders (oppositional defiant disorder and conduct disorder—ODD/CD), and daily reports of child oppositional and aggressive behaviour. We hypothesise that (a) child aggressive behaviour and prevalence of child externalising disorders will be significantly reduced at the post-assessment in the PLH-YC programme condition compared to the control condition; (b) these effects will be maintained over the long term (pre-intervention to follow-up change, post-intervention to follow-up stability of change); (c) past 24-h reports of child oppositional and aggressive behaviour as measured repeatedly between pre- and post-assessment will significantly decrease over the months of assessments in the PLH-YC condition compared to the control group.Test the effectiveness of the PLH-YC programme versus a parenting lecture on *secondary outcomes*, namely reductions in child internalising problems, dysfunctional parenting, child maltreatment, and parenting stress, as well as in improvements in daily reports of effective parenting behaviour, positive parenting, quality of parent-child relationship, parental mental health, and child quality of life. Based on the results of the previous phases, we also expect increases in parental relationship quality and decreases in intimate partner violence (physical and psychological victimisation and perpetration) in the parents’ relationship. We hypothesise that (a) there will be significant improvements in secondary outcomes at post-assessment to the advantage of PLH-YC; (b) these effects to be maintained at the follow-up assessment (pre-intervention to follow-up change, and post-intervention to follow-up stability of change); and that (c) past 24-h reports of effective parenting behaviours will significantly improve over the weeks of assessment in the PLH-YC programme condition compared to the control condition.

If the optimised programme is effective, a secondary objective of the RISE project is to explore the implementation and scalability of PLH-YC to enable wide-spread and sustained use of the optimised parenting programme in the Southeastern European countries. We will apply the steps of the RE-AIM model [38] to translate the learning from implementation of the evidence-based programme into sustainable practice. Moreover, we will report on the cost-effectiveness of the programme and other service use by parents in the PLH-YC and control conditions during, and after the intervention across the three countries.

The secondary aims and hypotheses are:
Examine the cost-effectiveness of PLH-YC in comparison to a lecture on parenting on the *primary outcome* of child aggressive behaviour and the economic impact of the programme, including potential costs for future dissemination and scale-up. Impact on other outcomes such as dysfunctional parenting, positive parenting, and child quality of life will also be used to better inform decision-making.To assess the role of socio-economic, contextual and individual factors (i.e. family adversity, parental mental health, intimate partner violence, couple dissatisfaction, and child aggressive behaviour at baseline) on the implementation of PLH-YC in the three countries. We will examine implementation in hypotheses a–c in two ways. We will examine these associations with enrolment (attended 1st session) across groups. We will also examine the associations with participation rate in the PLH-YC condition (percentage of sessions attended). The hypotheses are:
Higher family adversity at baseline assessment—including higher poverty, household hunger, parental mental health problems, intimate partner violence, and couple dissatisfaction will be associated with reduced participation in the PLH-YC group and lower enrolment across groups;Higher child aggressive behaviour at baseline will be associated with increased participation and enrolment by parents;Higher programme participation and enrolment will be associated with greater improvements in the primary and secondary outcomes;Higher programme fidelity and quality of delivery by facilitators of PLH-YC will be associated with greater improvements in the primary and secondary outcomes.We also hypothesise that indirect effects such that the above listed baseline variables (a and b) will predict enrolment, participation rate, and programme fidelity, which in turn will predict improvements in primary and secondary outcomes.*Additional Moderation Analyses*: Based on previous literature [27, 39, 40], we advance additional moderator hypotheses that pertain to parental, family, and child characteristics. Regarding parent/family characteristics, the hypotheses are as follows: (a) where parents have higher levels of baseline mental health problems, intervention effects on child aggressive behaviour will be greater in the PLH-YC compared to the control condition; (b) where parents have higher levels of baseline dysfunctional parenting, intervention effects on child aggressive behaviour will be greater for the PLH-YC condition compared to the control condition; (c) there will be no moderation effect of higher poverty, household hunger, and parental relationship dissatisfaction on the primary outcome child aggressive behaviour. The hypotheses related to child factors as moderators of intervention effect on the primary outcome are the following: (a) where children have higher levels of baseline child aggressive behaviour, intervention effects on aggressiveness will be greater, and (b) there will be no moderation effect of child gender or age on the primary outcome child aggressive behaviour (although gender may moderate outcome if associated with baseline level of child aggressive behaviour).

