### Study outcomes

#### Primary outcome

*Child aggressive behaviour* will be assessed with the respective subscale of the parent-report Child Behavior Checklist (CBCL) 1½–5 and 6–18 years old [43]. Parents rate the occurrence of certain behaviours of their child on a 3-point Likert Scale (0 = *not true* to 2 = *very true* or *often true*).

*Child externalising disorders* will be evaluated by using The Mini International Neuropsychiatric Interview for Children and Adolescents – Parent Version (MINI-KID-P) [44]. The MINI-KID-P will be used to assess whether the criteria (based on ICD-10 and DSM-5) for (a) Conduct Disorder (CD) (F91.1, F91.2, F91.9) or (b) Oppositional Defiant Disorder (ODD) (F91.3) are met (yes/no). The results of the two disorders will be combined to one binary total score with 0 = *no externalising disorder* and 1 = *current externalising disorder* (ODD or CD).

On three occasions between baseline and post-test assessments, Parent Daily Ratings (PDR) [45] will be used to monitor *child oppositional and aggressive behaviour problems* that occurred within the last 24 h (answer format: *did occur/did not occur*). In order to minimise drop-outs, we will only administer the oppositional and aggressive subscale (10 items + 2 positive items) instead of the full PDR. We excluded the last item from the subscale (“he/she pouts”) because this question caused translation problems in the three implementation countries. The item was not understood correctly by parents and assessors and thus did not result in valid answers. The PDR will be assessed over the phone three times between pre- and post-assessment.

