##### Primary and secondary outcome analyses

Data will be analysed using an intention-to-treat approach, in line with the study protocol and with good practice in RCTs [70]. Missing data will be handled using either multiple imputation or Full Information Maximum Likelihood (FIML) method [71].

The primary analysis will consist of testing comparatively the magnitude of change in child aggresive behaviour, in the control vs. PLH-YC participants, at post-test and follow-up. Identical analyses will be run for the secondary outcomes (i.e. child internalising problems, dysfunctional parenting strategies, positive parenting, daily reports of effective parenting behaviour, child maltreatment, parental mental health, IPV, couple satisfaction, parenting stress, quality of parent-child relationship, and child ’s quality of life). The main analyses will involve testing pre-post or pre-follow-up differences controlling for pre-intervention levels whilst accounting for covariates. Maximum likelihood estimation with robust statistics will be used with Mplus 8.2 software to account for non-normal distributions in measures and also apply a FIML framework for handling missing data at post- or follow-up. The models will be further tested using latent growth curve models adjusting for country and pre-assessment levels of the outcome variables (e.g. age as a time-invariant covariate). Indirect effect models will be tested in a structural equation framework and include participation rate and fidelity as mediators for the PLH-YC group and enrolment rate as the mediator across groups. In additional analyses, we will also model the effects of participation (i.e., attendance). This will be analysed with Complier Average Cause Effect models that estimate the magnitude of the paths based on the baseline scores in predictors (e.g. family adversity) and actual participation [72]. Further clustering will be within groups (facilitators) and included in subsequent analyses as needed. The analyses for MINI-KID ODD/CD positive screen will be conducted with logistical regression models due to the categorical nature of the data. Depending on the distributions and on other descriptive indicators, Bayesian analyses will be used as deemed appropriate.

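### The protocol is inconsistent about which measure and which time point decide the trial, and its sample-size calculation does not cover the binary primary measure

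*Protocol article*

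**What the plan says.** Three measures carry the primary label. In Overview and aims, the primary outcome is "child oppositional aggressive behaviour assessed by parent report of the level of child aggressive behaviour, prevalence of child externalising disorders", followed by daily reports of the child's behaviour. The Primary outcome section lists CBCL aggressive behaviour, then externalising disorders, which "will be evaluated by using The Mini International Neuropsychiatric Interview for Children and Adolescents" (a yes/no score), then the PDR: "The PDR will be assessed over the phone three times between pre- and post-assessment". The list is not ranked.

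The hypotheses follow this structure. Hypothesis (a) expects that "child aggressive behaviour and prevalence of child externalising disorders will be significantly reduced at the post-assessment". Hypothesis (b) adds that "these effects will be maintained over the long term (pre-intervention to follow-up change, post-intervention to follow-up stability of change"). Hypothesis (c) concerns the PDR trajectory.

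Other places point to one measure. The abstract states: "The primary outcome will consist of parent report of child oppositional aggressive behaviour". Primary and secondary outcome analyses states: "The primary analysis will consist of testing comparatively the magnitude of change in child aggresive behaviour", and applies this at both post-test and follow-up. The secondary aims and moderation hypotheses also call child aggressive behaviour the primary outcome, and Cost-effectiveness analysis uses the CBCL aggressive subscale.

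Sample size calculation refers to primary outcomes in the plural. It uses one effect size (d = .25, equated to f = .10), one alpha of .05, 80% power and a repeated measures ANOVA over three time points. It arrives at 704 analysed and 864 recruited. The binary measure is analysed differently: "The analyses for MINI-KID ODD/CD positive screen will be conducted with logistical regression models".

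**The concern.** A protocol should let a reader say, before the data are seen, which result makes the trial positive. Here the answer depends on the section consulted. Under the aims and the outcome list, a positive MINI-KID or PDR result with a null CBCL result could be presented as success on the primary outcome. Under the primary-analysis sentence the same data would be a failure. The same ambiguity arises if CBCL differs at 12 months but not at four, or the reverse.

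Two things are at stake. One is the type I error of the main claim, which depends on how many tests can each deliver success. The other is the meaning of the 80% power statement, which is attached to several outcomes although it can describe only a continuous one measured at pre, post and follow-up. MINI-KID is binary, and PDR is collected only between pre and post.

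**Working it through.** **The plan's own figure.** With two-sided alpha .05 and 80% power, a two-group comparison of means needs n per arm = 2(1.960 + 0.842)²/d². For d = .25 this is 252 per arm, 504 in total; for d = .20 it is 393 per arm, 786 in total. For two equal groups f = d/2, so d = .25 corresponds to f = .125, and f = .10 to d = .20. A repeated measures ANOVA with two groups, three time points and an assumed correlation of .5 gives 526 (between effect, f = .10), 338 (between, f = .125) or 164 (interaction, f = .10). None is 704. The repeated-measures correlation is not stated, so 704 cannot be verified; it is not proven wrong. Dropout: 704/0.83 = 849, close to 864. I take 704/2 = 352 per arm below and ignore clustering by group.

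**Number of tests.** Reading the aims literally: CBCL at post-test and follow-up (2), MINI-KID at post-test and follow-up (2), PDR trajectory (1), which makes five. The three measures without the follow-up tests make three. CBCL alone at both time points makes two.

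**Family-wise error if any one test suffices.** Assumptions: each test at two-sided .05, all nulls true, any single significant result counts. For independent tests the error is 1 − .95^k. Correlated cases come from 400,000 simulated multivariate normal draws with equal pairwise correlation.

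| Tests | r = 0 | r = .3 | r = .5 | r = .7 |
|---|---|---|---|---|
| 2 | 9.8% | 9.5% | 9.1% | 8.3% |
| 3 | 14.3% | 13.4% | 12.5% | 10.9% |
| 5 | 22.6% | 20.8% | 18.3% | 14.8% |

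Counting only false results in favour of PLH-YC roughly halves these. Five tests give 1 − .975^5 = 11.9% at r = 0 and 7.4% at r = .7; three tests give 7.3% to 5.5%. The benchmark for one two-sided test is 2.5%.

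**Power for the binary measure.** The protocol gives no control prevalence and no target difference, so both are assumed. Converting d = .25 to an odds ratio: exp(.25 × π/√3) = 1.57. For control prevalence p, the intervention odds are p/(1 − p) divided by 1.57. Example: p = .40 has odds .667; .667/1.574 = .424, a prevalence of .298. Power for two proportions with 352 per arm:

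| Control prevalence | 10% | 20% | 30% | 40% | 50% | 60% | 70% | 80% |
|---|---|---|---|---|---|---|---|---|
| Power | 37% | 61% | 74% | 82% | 85% | 85% | 82% | 73% |

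With the d = .20 equivalent (odds ratio 1.44), which is what f = .10 implies, power runs from 27% to 67% over the same prevalences.

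**Power with one primary.** A simple two-group comparison of CBCL at one time point, 352 per arm: .25 × √(352/2) = 3.32; 3.32 − 1.96 = 1.36, so power is 91%. At d = .20 it is 76%.

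**The case against.** The strongest reply is that the text does indicate a lead measure. The Primary outcome section defines child aggressive behaviour as the CBCL subscale, and the primary-analysis sentence, the secondary aims and the cost-effectiveness section all use that term. PDR cannot enter a test at post-test and follow-up, because it is not collected then. This stands: a reader might infer that there is no hierarchy at all, and that would be too strong. The fault is that this informal lead conflicts with the aims and the outcome list, and that even the primary-analysis sentence leaves two time points unranked.

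A reader might also take 15–23% as the trial's actual error rate. The documents do not support that. No any-one-of-five rule is stated; alpha appears only in the sample-size paragraph; hypothesis (a) joins its two measures with an and, and requiring both would not inflate the error; hypothesis (b) is worded as maintenance of an effect already shown. The upper end also needs independent tests, whereas all three measures are parent reports on related behaviour.

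A multiplicity procedure may sit in an analysis plan that is not shown, and its absence here is not the point. The identity of the primary endpoint belongs in the protocol, and this protocol gives conflicting answers.

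Finally, a reader might infer that MINI-KID is underpowered. At the d = .25 equivalent, power reaches 80% or more for control prevalences of about 40% to 70%. Children are selected for at least subclinical ODD scores, so prevalences in that range cannot be ruled out.

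**Conclusion.** The inconsistency is real and should be resolved. The aims and the outcome list make three measures primary, and the sample-size section speaks of primary outcomes in the plural. The abstract, primary-analysis sentence and cost-effectiveness section treat child aggressive behaviour as primary, and no section says whether post-test or follow-up decides.

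The size depends on the reading. Under the most permissive one (any of five tests, two-sided .05 each, correlations .7 to 0), family-wise error is about 15–23%, or 7–12% for false benefit. Under the narrowest one (CBCL only, two time points) it is at most 9.8% two-sided. Every reading in which one of several tests suffices exceeds 5%, but the text does not establish which reading applies.

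The sample-size calculation does not address the binary measure. Whether MINI-KID is underpowered depends on a control prevalence and an effect that the protocol does not give.

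**What to change.** Bring Overview and aims, Primary outcome and Sample size calculation into line with the primary-analysis sentence:

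- Name CBCL aggressive behaviour at one stated time point as the single primary endpoint. Post-test fits hypothesis (a), with follow-up worded as maintenance; the choice is the sponsor's, but it has to be one.
- Test CBCL at the other time point and then MINI-KID in fixed sequence at .05, or label them secondary.
- Make PDR secondary.
- State that the power figure applies to CBCL only.

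If several primaries are preferred, the alpha must be split. At d = .25 in a simple comparison, three tests at .0167 need 672 analysed (82% power with 704); five at .01 need 748 (77% with 704).

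The preferred change needs wording only, in the protocol, analysis plan and registry entry, and no extra participants. Its cost is that a positive MINI-KID or PDR result after a failed CBCL test can no longer be called a primary success. Timing matters: Trial status reports post-assessments completed on September 24, 2021. The choice should therefore be documented, dated and made before anyone sees outcome data by arm; otherwise it is open to the criticism that it was made with knowledge of the results.
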